## Abstract

**Background**: Chronic low back pain (CLBP) is a common musculoskeletal disorder that significantly impairs quality of life and is frequently associated with vitamin D deficiency. Therapeutic exercise is a cornerstone of management, yet the optimal adjunct intervention to restore serum vitamin D levels remains uncertain. No prior randomized trial has compared oral vitamin D supplementation with lifestyle education on sun exposure, nutrition, and physical activity, both combined with therapeutic exercise. We hypothesize that therapeutic exercise plus an education booklet (TEB) may be superior to therapeutic exercise plus oral vitamin D supplementation (TED) in reducing pain and disability while improving serum vitamin D levels.

**Methods**: This assessor-blinded, two-arm, multicenter randomized controlled trial (RCT) will be conducted in hospitals and rehabilitation centers in Dhaka city, Bangladesh. Adult participants (18–65 years) with CLBP and confirmed vitamin D deficiency will be recruited and randomized to either TEB or TED groups. Both groups will receive standardized therapeutic exercise protocols. The intervention duration will be 6 months, with assessments at baseline, 2 months, and 6 months. Primary outcomes include pain intensity measured by the Brief Pain Inventory (BPI) and serum 25(OH)D3 levels. Secondary outcomes include disability assessed by the Roland-Morris Disability Questionnaire (RMDQ). Statistical analysis will follow the intention-to-treat principle, using repeated measures ANOVA to compare group differences over time.

**Discussion**: This trial will provide evidence on whether a multidimensional lifestyle-based education approach combined with therapeutic exercise offers greater benefit than vitamin D supplementation with exercise in CLBP patients with vitamin D deficiency. The findings will inform clinical guidelines and support comprehensive management strategies for CLBP, particularly in resource-limited settings.

Registration: Clinical Trials Registry India (
CTRI/2022/11/047074).

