### Eligibility criteria

Participants will be included if they present with chronic low back pain (CLBP) of central origin, persisting for more than three months and classified under ICD-10-CM Code M54.5, with documented vitamin D deficiency defined as serum 25(OH)D3 levels below 20 ng/mL.
^
16
^ Eligible individuals must be adults aged 18 years or older, of either gender, residing or working in Dhaka city in office, industry, or corporate settings that involve static postures or desk jobs requiring at least six hours of sitting per day for an average of 22 days per month, and must provide informed consent. Exclusion criteria comprise comorbid conditions that may influence vitamin D metabolism or bone health, including rheumatoid arthritis, ankylosing spondylitis, osteomalacia, tuberculosis of the spine, or a history of osteoporotic fracture. Women over 50 years of age or those who are post-menopausal will also be excluded,
^
14
^ as will individuals with prior use of calcium or vitamin D3 supplements, resistance training, or high-impact weight-bearing activities within the past six months. Patients presenting with neurological red flags such as dural signs, positive straight leg raise test, or bowel/bladder incontinence will not be considered. Additional exclusions include current participation in another clinical study and withdrawal during the 8-week intervention period.

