**Booklet contents (B):**
^
24–
26
^

The educational booklet provides lifestyle and self-management advice designed to complement therapeutic exercise. Key recommendations include:
•Avoid prolonged static sitting or standing; alternate between sitting and standing during work.•Consume natural sources of vitamin D3 such as milk, yogurt, fortified cereals, orange juice, mushrooms, margarine, hard-boiled eggs, and sea fish (e.g., tuna, salmon).•Engage in 30–35 minutes of sun exposure between 11:00 am and 2:00 pm.•Maintain 7–8 hours of sleep per night.•Avoid stress, smoking, and alcohol consumption, while maintaining a healthy body weight.•Perform regular physical activity as part of daily routine.

Therapeutic exercise protocol (TE):
^
27–
29
^

Both groups will receive therapeutic exercises. Exercises will focus on both back pain and disability minimization of the participants. Each session will last for 25-30 minutes, 4 days per weeks and for 8 weeks. The progression of therapeutic exercise will be as per the registered protocol. Exercises are delivered under a physiotherapist supervision and include:
•Postural advice (TH.1): Maintain erect posture in sitting and standing; avoid prolonged sitting/standing and forward bending.•McKenzie’s directional preference exercises (TH.2): Sustained positioning and repeated movements, most often extension-based, performed in sets of 10 repetitions.•Stretching exercises (TH.3): Targeting erector spinae, hamstrings, and triceps surae muscles.•Lumbar stabilization exercises (TH.4): Core strengthening to enhance spinal stability.•Weight-bearing aerobic exercises (TH.5): Jogging, stair climbing, and 30 minutes of brisk walking.•Heating modalities (TH.6): Infra-red radiation applied as adjunct therapy.

Vitamin D supplementation (D):

Participants in the TED group will receive 40,000 IU vitamin D3 capsules once weekly for 8 weeks, prescribed by a registered physician and manufactured by a licensed pharmaceutical company in Bangladesh.
^
23
^

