We expect there will be no major adverse effect for therapeutic exercise and booklet group and that there will be no request of dosage change or worsening of patients’ condition. If any of these occur we will discuss with the patient. If the patient is not willing not to continue, we will stop the intervention, and keep the data for intention to treat analysis. The vitamin D supplement group may experience some adverse effect; we will manage as per the standard measures described in the “safety measures” section. The adherence to these interventions will be monitored through checklist (Extended data 1
^
37
^). We will also monitor adverse effect using a checklist (Extended data 2
^
37
^).

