## Participant timeline

### Sample size

The sample size for this trial was determined based on methodological standards used in low back pain research. Previous studies have indicated that randomized controlled trials in chronic low back pain require a minimum of 152 participants to detect clinically meaningful superiority differences, with a significance level (α) of 0.05, statistical power of 80%, and a 95% confidence interval. Considering potential attrition, we plan to recruit additional participants to ensure adequate statistical power and robustness of findings.
^
34,
35
^

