### Recruitment and study procedure

We will follow the Consolidated Standards of Reporting Trials (CONSORT) to maintain the standards of the study procedure (
Figure 1). For the initial recruitment the LBP patients attending outdoor clinics of both centers from 1st December 2022 to 30th May 2022 will be primarily screened by the outdoor team and provided participant information sheet (PIS) of the study. The final screening will be performed by two licensed physician specializing in physical medicine and rehabilitation. These physicians held postgraduate qualifications (MD/MS in Rehabilitation Medicine or Orthopedics) and had a minimum of 5–10 years of clinical experience in musculoskeletal disorders and pain management. The patient will meet the blinded assessor who will then take pretest data in a separate room, and collect a blood sample, before returning the patient to the outdoor pool. From outdoor pool, the patient will have a concealed envelop with another random ID number matched by the initial ID number given and meet the intervention provider (physiotherapist and physician or physiotherapist alone). Patient will receive the intervention provided in the written guideline enclosed in the concealed envelope. After 8 weeks of treatment completion, the patient will be further screened by blinded assessor, and another blood sample will be collected before discharge. After six months, the patient will be invited to the treatment center or visited in their house or workplace for follow up evaluation and blood sample collection. Therapeutic exercise will be provided by a graduate physiotherapist, and medication will be provided by a registered medical practitioner. Patient will pay for the physiotherapy treatment sessions but will not pay for any additional blood tests, medication or booklet.

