### Data analysis

Data will be analyzed based on its nature. Calculation and data auditing will be done using Microsoft Excel 2016. Data will be analyzed by SPSS version 23, and R-4.2.1 for Windows. Eligibility for parametric analysis will be checked using bell’s curve, skewness, kurtosis, Kolmogorov–Smirnov test and Shapiro–Wilk test. Continuous variables will be represented by using an arithmetic mean and standard deviation. Categorical data will be represented by percentage (%) and frequency. Baseline characteristics between groups will be compared using chi-square tests for categorical variables and independent t-tests or Mann–Whitney U tests for continuous variables, depending on data distribution. Normality will be assessed using the Shapiro–Wilk test. For within-group comparisons across time points (baseline, 2 months, and 6 months), repeated measures ANOVA will be applied for parametric data, with Greenhouse–Geisser correction if sphericity is violated; the Friedman test will be used for non-parametric data. Between-group differences over time will be analyzed using mixed-model repeated measures ANOVA, which accounts for group × time interactions, or generalized estimating equations (GEE) if assumptions are not met. Post-hoc pairwise comparisons will be adjusted using Bonferroni correction. Effect sizes (Cohen’s d or partial eta squared) will be reported to indicate the magnitude of differences. All analyses will be conducted at a two-tailed alpha level of 0.05, and intention-to-treat principles will be applied to handle missing data.

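### Withdrawal during the 8-week treatment period is listed as an exclusion, which can only remove randomised patients and contradicts the intention-to-treat commitment

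*Protocol article*

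**What the plan says.** - **Eligibility criteria**, last sentence: "Additional exclusions include current participation in another clinical study and withdrawal during the 8-week intervention period".
- **Interventions**, therapeutic exercise protocol: "Each session will last for 25-30 minutes, 4 days per weeks and for 8 weeks". The vitamin D capsules also run for 8 weeks, so this is the treatment period in both arms.
- **Recruitment and study procedure**: screening, baseline assessment and blood sample come first, then the envelope. After that, "Patient will receive the intervention provided in the written guideline enclosed in the concealed envelope".
- **Abstract**: "Statistical analysis will follow the intention-to-treat principle".
- **Data analysis**: "intention-to-treat principles will be applied to handle missing data".
- **Interventions**, closing paragraph on adverse effects: "If the patient is not willing not to continue, we will stop the intervention, and keep the data for intention to treat analysis". From the context, the first part is meant to describe a patient unwilling to go on.
- **Sample size**: "Considering potential attrition, we plan to recruit additional participants", with no rate given.
- **Recruitment and study procedure**, on the 6-month assessment: "the patient will be invited to the treatment center or visited in their house or workplace for follow up evaluation".

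**The concern.** An eligibility criterion has to be something that can be judged before allocation. Withdrawal during treatment cannot be, so listing it as an exclusion makes an event after randomisation a reason to treat a randomised patient as never eligible. Intention-to-treat requires the opposite: the patient stays in the allocated group, and any missing outcome is handled as missing.

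Two things are at stake. The first is precision, if patients who stopped treatment but could still be assessed are discarded. The second is bias, if withdrawal is related to outcome and differs between arms. Patients and physiotherapists are not blinded (Randomization), the two arms are treated at different institutions (Study setting), and Interventions foresees possible adverse effects in the vitamin D arm but no major ones in the booklet arm. Unequal withdrawal is therefore possible. The documents do not show that it will occur: both arms have the same 4 × 8 = 32 exercise sessions, patients in both pay for them, and the safety section expects no harm from supplementation or exercise.

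**Working it through.** **Step 1: order of events.** Recruitment and study procedure gives the order as screening, baseline data, envelope, treatment. A withdrawal in the 8 treatment weeks comes after the envelope, so the clause can apply only to randomised patients.

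**Step 2: is there a reconciling sentence?** Nothing limits the clause to a per-protocol set, and nothing says that withdrawers' data are still analysed. The nearest candidate is the keep-the-data sentence in Interventions. Read literally, it follows the booklet-group sentence and is triggered only by the events listed there (a major adverse effect, a request to change dosage, worsening). On that reading it leaves other withdrawals without a rule. Read broadly, it contradicts the clause directly. If withdrawal means leaving the trial altogether (the sense used in the ethics section), the two sentences concern different events, and the conflict with the Abstract and Data analysis remains.

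**Step 3: size, for illustration.** The plan has no figure of its own to reproduce: it states 152 participants, two-sided α = 0.05 and 80% power, but no effect size, SD or withdrawal rate. Assumptions made here:
- exactly 152 randomised, 76 per arm, ignoring the unquantified extra recruitment;
- a two-sample t-test as a stand-in for the planned repeated-measures model;
- withdrawal p of 10% or 20%;
- a share f of withdrawers who would still supply outcomes.

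At 76 per arm, 80% power corresponds to a difference of 0.457 SD.

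Analysed with the clause: 152(1 − p). Without it: 152(1 − p(1 − f)). Discarded by the clause: 152pf.

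| p (both arms) | f | Analysed without → with clause | Discarded | Power without → with |
|---|---|---|---|---|
| 10% | 0 | 136.8 → 136.8 | 0 | 75.7% → 75.7% |
| 10% | 0.5 | 144.4 → 136.8 | 7.6 | 77.9% → 75.7% |
| 10% | 1 | 152 → 136.8 | 15.2 | 80.0% → 75.7% |
| 20% | 0 | 121.6 → 121.6 | 0 | 70.6% → 70.6% |
| 20% | 0.5 | 136.8 → 121.6 | 15.2 | 75.7% → 70.6% |
| 20% | 1 | 152 → 121.6 | 30.4 | 80.0% → 70.6% |

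**Step 4: bias.** Let withdrawers do δ SD worse than those who stay, and set the stayers' mean to 0. Without the clause, an arm's mean is −δpf/(1 − p + pf). With it, the mean is 0. The shift due to the clause is the difference between arms in that quantity.

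For 10% against 20% withdrawal:
- f = 0: shift 0.
- f = 0.5, δ = 0.5: 0.0556 − 0.0263 = 0.029 SD. With δ = 1.0: 0.1111 − 0.0526 = 0.058 SD.
- f = 1, δ = 0.5: 0.10 − 0.05 = 0.05 SD. With δ = 1.0: 0.20 − 0.10 = 0.10 SD.

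The shift favours the arm that loses more patients. With equal withdrawal and equal prognosis in both arms it is zero for every f.

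**The case against.** The best defence is that this is a stopping rule filed under the wrong heading. The eligibility section names no analysis set, and every sentence that does address analysis points to intention-to-treat. On either meaning of withdrawal the harm may also be small. Patients who leave the trial supply few outcomes anyway, which is the f = 0 row with no cost. Patients who only stop treatment may be covered by the keep-the-data sentence, and its mention of a dosage change suits capsules at least as well as a booklet, so the narrow reading of that sentence is open to doubt.

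Part of this stands. The text does not prove an intention to drop patients, the consequences rest on assumed rates, and f may well be nearer 0 than 1. But the benign reading appears nowhere in the eligibility section, which calls withdrawal an exclusion. Even a patient who leaves with only baseline data must be counted under intention-to-treat, not reclassified as ineligible. Nor is this detail that an analysis plan would supply: the article states two incompatible rules, and whoever writes the analysis plan would have to choose between them.

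It is also fair to note that the 8-week visit is described as following completion of treatment, so a visit for someone who stopped early is not spelled out there. Table 1, however, schedules all three outcomes at 2 and 6 months without that condition.

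**Conclusion.** The concern holds. The contradiction is textual and needs no assumption: an exclusion that can operate only after randomisation is incompatible with the stated intention-to-treat analysis. Its effect on the trial cannot be determined from the documents. Under the assumptions above, the clause costs between nothing and 9.4 percentage points of power (80.0% to 70.6%) and shifts the treatment difference by 0 to 0.10 SD. Both are zero if no withdrawer could be assessed, and the shift is also zero if withdrawal and prognosis are the same in both arms. The protocol itself expects attrition, so the clause would probably have patients to act on. It should be corrected, with high confidence in the conflict and much less in any particular size.

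**What to change.** Delete the withdrawal clause from the exclusion criteria. State once, for both arms and for any reason for stopping:
- all randomised patients are analysed in the group to which they were randomised;
- data already collected are kept;
- the 2- and 6-month assessments are still sought after treatment stops, counted from baseline and not conditional on completing treatment, unless the patient withdraws consent to follow-up.

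Replace the keep-the-data sentence in Interventions with this rule. If an analysis of patients who completed the 8 weeks is wanted, label it per-protocol and secondary.

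The cost is a wording amendment, with the notice to the review board and registry that the ethics section already promises. It needs no extra patients, and the assessments fall at time points already in Table 1.

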### Interventions

Participants will receive interventions according to the registered study protocol, consisting of either therapeutic exercise combined with an educational booklet (TEB) or therapeutic exercise combined with oral vitamin D3 supplementation (TED).
^
23
^

**Booklet contents (B):**
^
24–
26
^

The educational booklet provides lifestyle and self-management advice designed to complement therapeutic exercise. Key recommendations include:
•Avoid prolonged static sitting or standing; alternate between sitting and standing during work.•Consume natural sources of vitamin D3 such as milk, yogurt, fortified cereals, orange juice, mushrooms, margarine, hard-boiled eggs, and sea fish (e.g., tuna, salmon).•Engage in 30–35 minutes of sun exposure between 11:00 am and 2:00 pm.•Maintain 7–8 hours of sleep per night.•Avoid stress, smoking, and alcohol consumption, while maintaining a healthy body weight.•Perform regular physical activity as part of daily routine.

Therapeutic exercise protocol (TE):
^
27–
29
^

Both groups will receive therapeutic exercises. Exercises will focus on both back pain and disability minimization of the participants. Each session will last for 25-30 minutes, 4 days per weeks and for 8 weeks. The progression of therapeutic exercise will be as per the registered protocol. Exercises are delivered under a physiotherapist supervision and include:
•Postural advice (TH.1): Maintain erect posture in sitting and standing; avoid prolonged sitting/standing and forward bending.•McKenzie’s directional preference exercises (TH.2): Sustained positioning and repeated movements, most often extension-based, performed in sets of 10 repetitions.•Stretching exercises (TH.3): Targeting erector spinae, hamstrings, and triceps surae muscles.•Lumbar stabilization exercises (TH.4): Core strengthening to enhance spinal stability.•Weight-bearing aerobic exercises (TH.5): Jogging, stair climbing, and 30 minutes of brisk walking.•Heating modalities (TH.6): Infra-red radiation applied as adjunct therapy.

Vitamin D supplementation (D):

Participants in the TED group will receive 40,000 IU vitamin D3 capsules once weekly for 8 weeks, prescribed by a registered physician and manufactured by a licensed pharmaceutical company in Bangladesh.
^
23
^

We expect there will be no major adverse effect for therapeutic exercise and booklet group and that there will be no request of dosage change or worsening of patients’ condition. If any of these occur we will discuss with the patient. If the patient is not willing not to continue, we will stop the intervention, and keep the data for intention to treat analysis. The vitamin D supplement group may experience some adverse effect; we will manage as per the standard measures described in the “safety measures” section. The adherence to these interventions will be monitored through checklist (Extended data 1
^
37
^). We will also monitor adverse effect using a checklist (Extended data 2
^
37
^).

**Outcome measurement**

**
*Primary outcome*
**

*Pain*

The BPI (Brief Pain Inventory), comprising fifteen items, evaluates the degree of pain and how it affects everyday living. It measures pain interference in relationships, emotions, quality of life, and physical activities, including sleep, general activity, and walking; it also contains pain diagrams and questions regarding drugs and analgesics. Higher ratings indicate more acute pain and more interference.
^
30
^ With an interclass correlation coefficient (ICC) of 0.84–0.90 and kappa values over 0.70, the BPI exhibits great internal consistency (Cronbach's alpha = 0.91) and dependable test–retest results.
^
10
^

*Vitamin-D3 level*

Serum 25(OH) D will be used to measure the level of Vitamin D3. Tests will be advised by an expert physician, and researchers will collect information from laboratory test reports. Patients will be categorized based on vitamin D levels, such as deficient (less than 20 ng/mL); insufficient (21 to 29 ng/mL); and sufficient (more than 30 to 100 ng/mL).
^
10,
31
^

**
*Secondary outcome*
**

*Disability*

The RMDQ (Roland–Morris Questionnaire) is a 24-item patient-reported instrument that is intended to evaluate pain-related impairment resulting from LBP. Every item has a value of 0 if left blank or 1 if approved, therefore producing a total score between 0 and 24, with higher scores denoting greater impairment.
^
32
^ Whereas absolute reliability (Standard Error of Measurement, SEM) is estimated between 1.7 and 2.0 points, test-retest reliability usually falls within an intra-class correlation range of 0.79-0.88.
^
33
^

## Participant timeline

### Sample size

The sample size for this trial was determined based on methodological standards used in low back pain research. Previous studies have indicated that randomized controlled trials in chronic low back pain require a minimum of 152 participants to detect clinically meaningful superiority differences, with a significance level (α) of 0.05, statistical power of 80%, and a 95% confidence interval. Considering potential attrition, we plan to recruit additional participants to ensure adequate statistical power and robustness of findings.
^
34,
35
^

